### Intervention

Therapists of the intervention condition have been trained in cultural competence. The training program is based on existing modules that are widely used in the Netherlands and are based on international and national literature [18-23]. The aim of the module is to train the intervention therapists' knowledge, awareness and skills in diagnosing and treating Moroccan and Turkish patients with depression and anxiety disorders.

To improve the cultural knowledge the therapists are familiarized with the Moroccan and Turkish patients' background and learn about:

• the specific cultural aspect and elements,

• the impact of migration in first and second generation immigrants,

• the migration history,

• the religious background, (health)habits, beliefs, explanations and expectations,

• traditional health care and health workers.

To improve the cultural awareness therapists are taught to:

• be aware of their own cultural background, attitudes and values,

• recognise prejudices and generalizations regarding the cultural background of the patients.

To improve the intercultural skills the therapists are trained:

• how to give psychoeducation

• how to make use of an interpreter during treatment,

• how to make use of the Cultural Formulation [24] during intake and treatment,

• in intercultural diagnostics [25],

• how to use the intercultural addenda to the treatment guidelines for depression and anxiety disorders [26,27].

The module has an interactive character. It contains exercises in becoming aware of the therapists' own cultural background; a discussion about how to deal with traditional health workers; a role play with an actor in using an interpreter and in using the Cultural Formulation during treatment.

The training takes two days. After the training the intervention therapists join a monthly intercultural peer group to keep knowledge, awareness and skills vivid.

### Assessments

Data are collected at three points in time: within two weeks after the intake (T0), four weeks after the start of the treatment (T1), 16 weeks after the start of the treatment (T2). Table 1 summarizes the measures that are used at each point. The assessments are partly performed face to face by a trained interviewer and partly self report. Most of the interviewers are bilingual. Besides sufficient command of the Dutch language the Turkish, Moroccan-Arabic and Berber languages are requested respectively. The interviewers participate in a three day training. The interview and self report questionnaires consist of pen and paper versions only.

**Table 1 T1:** Summary of measures

Primary outcome measure	Measurement instrument	Method	Baseline	Follow-up 1	Follow-up 2
Dropout	Medical Record	Report- therapist		X	X

					

**Secondary outcome measure**	**Measurement instrument**	**Method**	**Baseline**	**Follow-up 1**	**Follow-up 2**

***Course of treatment***					
Type of treatment	Medical Record	Report- therapist		X	X
Time in treatment	Medical Record	Report- therapist		X	X
No-show	Medical Record	Report- therapist		X	X
***Patients' perspective of treatment***					
Therapeutic relationship	HAQ	Self Report- patient	X	X	X
Patient evaluation of trust in care	NIVEL	Self Report- patient	X		X

					

**Determinants**	**Measurement instrument**	**Method**	**Baseline**	**Follow-up 1**	**Follow-up 2**

***Demographics***	Standard questions	Interview- patient			
			X		
***Public Health consequences***					
Level of functioning	WHO-DAS II	Self Report- patient	X	X	X
Work productivity	TIC-P	Interview- patient	X	X	X
Need of care	PNCQ Meadows	Interview- patient	X		X
***Anxiety and Depression***					
Diagnosis	CIDI	Interview- patient	X		
Severity of depression	IDS	Self Report- patient	X	X	X
Severity of anxiety	BAI	Self Report- patient	X	X	X
***Physical Conditions***					
Somatic disease	One- question	Interview- patient	X	X	X
Medication use	Medication use Questionnaire	Interview- patient	X		X
Pain	Chronic graded pain scale	Interview- patient	X		X
***Social functioning***					
Acculturation	LAS	Interview- patient	X		
Discrimination	Part of the National Survey of Midlife Development in US	Interview- patient	X		
Social functioning	Close Person Inventory	Self Report- patient	X		X

### Primary outcome measure

The primary outcome measure is drop-out of treatment. Treatment drop-out is defined as: the patient is in need of more therapy in the therapist's opinion but ignores at least two invitations of the therapist and does not continue the sessions. Data will be gathered by interviewing the therapists and analysing the medical records.

### Secondary outcome measures

Secondary outcome measures focus on no-show and the patients' perspective of treatment. No-show rates will be collected from the medical records of the participants. The patients' perspective will be measured using the Helping Alliance Questionnaire [28] and the trust in mental health care questionnaire (a part of the NIVEL consumer panel questionnaire will be used [29]).

### Dropout determinants

Several possible determinants of drop-out will be explored:

Demographic factors (age, gender, marital status, education); level of functioning (WHO-Disability Schedule II (WHO-DAS II) [30]); loss of productivity at work and health care utilization (Trimbos/iMTA questionnaire for costs associated with psychiatric illness (TIC-P) [31]); perceived need for care (Perceived Need for Care questionnaire (PNCQ) [32]); the diagnosis of depression and anxiety disorders (Composite International Diagnostic Interview (CIDI) depression and anxiety life time version (WHO version 2.1) ([33,33,35]); severity of depressive symptoms (Inventory of Depressive Symptoms self report version (IDS) [36]); severity of generalised anxiety and panic symptoms (Beck Anxiety Inventory self-report version (BAI)[37]); somatic disease (perceived somatic problems on an analogue scale from 1 to 10); medication use (Medication use questionnaire); pain (Chronic graded pain scale [38]); acculturation (the Lowlands Acculturation Scale (LAS) [39,40]); social support (Close Person Inventory [41]); discrimination (a part of the national survey of Midlife development in the US); locus of control (Pearlin and Schooler mastery scale [42]).

### Translation of the instruments

For this project insufficient command of the Dutch language is not an exclusion criterion. Therefore, we use translated questionnaires if necessary. For respondents who only understand the Turkish language, we use translated and validated Turkish instruments (IDS http://www.ids-qids.org, BAI [43], CIDI (WHO)) and translated instruments used in the Amsterdam Health Monitor (AHM) study [44] (Who-Das II, PNCQ, LAS, discrimination, locus of control, NIVEL trust in care). The other questionnaires were translated at our institute. Bilingual (Dutch and Turkish speaking and writing) mental health professionals translated the Dutch version into Turkish and this Turkish version was translated back into Dutch by other bilingual mental health professionals.

Because the Moroccan language is a collection of dialects no validated and translated versions of the instruments are available. For the respondents who only understand a Moroccan language we use several instruments used in the Amsterdam Health Monitor (AHM) (CIDI, LAS, discrimination, locus of control, PNCQ). These instruments were not completely translated into Moroccan Arabic. The Dutch version is used and only a keyword in each question was translated into Moroccan Arabic. For the other interview instruments (demographic, TIC-P, medication use, somatic disease, pain scale) keywords were translated in our institute by a focus group of bilingual students (Dutch-Moroccan-Arabic). For the self-report a complete translated version into Moroccan Arabic is accomplished. We asked the Dutch public translation centre (Tolk Vertaal centrum Nederland or TVcN) to translate the Dutch instruments into modern standard Moroccan Arabic. A focus group of bilingual students (Dutch-Moroccan-Arabic) translated it back into Dutch and adapted the Moroccan translation where necessary. We knew from the AHM study that most of the Moroccan respondents who did not speak Dutch well enough, speak a mix of Berber, Moroccan Arabic and Dutch. The interviewers are trained to cope with these language problems as much as possible. In all interviews the interviewers will specify in which language the interview has been conducted and how many problems they have encountered (language or verbal expression problems, associative behaviour or reluctancy to answer). Interviewers assess the reliability of the answers given.

### Sample size

No comparable intervention studies, aiming to reduce drop-out rates in immigrants, have been found in literature. In an intervention study by Blom et al [11,12], post hoc analyses showed that the drop-out rate was 46% in immigrant patients compared to 24% in native patients. Based on these data we assume that the drop-out can be reduced from 45% to 30%, an improvement of 33%. To demonstrate this difference 75 patients in each condition (beta 0.01 and alpha 0,05) should be included [45].

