****Methods/Design**:**

A randomized clinical trial was started in January 2010. Moroccan and Turkish adult patients who are referred to our outpatient clinics for mood and anxiety disorders are randomly assigned to mental health workers who are trained in a cultural module and to those who are not. The therapists have been trained in the Cultural Formulation and in techniques bridging the (cultural) gap between them and their Moroccan and Turkish patients.

The target number of participants is 150 patients, 75 for each group. Drop-out of treatment is the primary outcome measure. Secondary outcome measures are no-show and patients' perspective of care.

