### Analysis

Basic characteristics will be compared between treatment conditions. Dropout will be analysed by (non) parametric longitudinal analysis techniques (eg GLM model) using multivariate statistics. Determinants are modelled along. Analysis will be performed according to the intention-to-treat principle.

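### 75 patients per arm gives about 47% power (two-sided) for 45% versus 30% drop-out, not the 99% implied by beta 0.01

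*Protocol article*

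**What the plan says.** The Sample size section of the protocol article starts from an earlier intervention study in which "post hoc analyses showed that the drop-out rate was 46% in immigrant patients compared to 24% in native patients". From this it derives the design effect: "we assume that the drop-out can be reduced from 45% to 30%, an improvement of 33" per cent. It then fixes the size of the trial: "To demonstrate this difference 75 patients in each condition (beta 0.01 and alpha 0,05) should be included". The Methods/Design part of the abstract repeats the number: "The target number of participants is 150 patients, 75 for each group".

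The endpoint is binary: "The primary outcome measure is drop-out of treatment". The Analysis section says: "Dropout will be analysed by (non) parametric longitudinal analysis techniques (eg GLM model) using multivariate statistics". The sample-size text names no test, no sidedness, no correlation between repeated measurements and no allowance for loss or for therapists.

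**The concern.** The demonstrative in the sample-size sentence can refer only to the fall from 45% to 30%, and the sentence attaches "beta 0.01 and alpha 0,05" to it. Beta is the probability of missing the effect if it is real, so the text claims that a true 15-point reduction would be missed once in a hundred trials. A 15-point difference between two proportions near 40% normally needs well over 100 patients per arm even for 80% power, so 75 per arm is implausible on its face.

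This is the only justification given for the size of the primary comparison. If the true power is near one half, the trial is about as likely to miss the assumed effect as to find it. A reader who believes the stated beta would take a non-significant result as near-proof that the training does not work. The Background says there is so far no evidence that such training reduces drop-out, so a misread null result could carry undue weight.

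**Working it through.** **Inputs, all from the Sample size section:** p1 = 0.45, p2 = 0.30, difference d = 0.15, n = 75 per arm (1:1), alpha = 0.05, beta = 0.01. Sidedness is not stated; two-sided is taken as the default and one-sided is also shown.

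**Formula** (two proportions, pooled variance under the null):

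n per arm = [z_alpha × A + z_power × B]² / d², where A = √(2 p̄(1 − p̄)) and B = √(p1(1 − p1) + p2(1 − p2)).

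Here p̄ = 0.375, A = √(2 × 0.375 × 0.625) = 0.6847 and B = √(0.2475 + 0.2100) = 0.6764.

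**1. Attempt to reproduce 75 per arm.** With z_alpha = 1.960 (two-sided):

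- 99% power: (1.3419 + 2.3263 × 0.6764)² / 0.0225 = 2.9154² / 0.0225 = 377.8, so 378
- 90% power: (1.3419 + 1.2816 × 0.6764)² / 0.0225 = 2.2087² / 0.0225 = 216.8, so 217
- 80% power: (1.3419 + 0.8416 × 0.6764)² / 0.0225 = 1.9112² / 0.0225 = 162.3, so 163

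The stated 75 is about one fifth of 378. With z_alpha = 1.645 (one-sided) the requirements are 324, 177 and 128. None is near 75.

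**2. Power at 75 per arm.** Power = Φ[(d√n − z_alpha × A) / B].

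- Two-sided: (0.15 × √75 − 1.3419) / 0.6764 = (1.2990 − 1.3419) / 0.6764 = −0.063, so power = 47.5%
- One-sided: (1.2990 − 1.1262) / 0.6764 = 0.256, so power = 60.1%

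Other methods give the same picture (two-sided):

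| Method | Power at 75 per arm |
|---|---|
| Unpooled variance | 48.4% |
| Arcsine | 47.9% |
| Continuity-corrected | 40.7% |
| Chi-square, exact enumeration | 48.6% |
| Fisher's exact test, exact enumeration | 41.9% |

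**3. What 75 per arm can detect.** With a 45% control rate and a two-sided test, the intervention rate must be about 23.5% for 80% power, 20.5% for 90% and 14.1% for 99%. The first is slightly below the 24% reported for native patients, so the training would have to close the whole gap.

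**4. Precision.** The 95% half-width for the risk difference is 1.96 × √(0.2475/75 + 0.2100/75) = 1.96 × √0.0061 = 0.153. That is 15.3 points, about equal to the assumed effect of 15 points.

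**5. A possible origin of the number.** For 46% versus 24% (A = 0.6745, B = 0.6564, d = 0.22), 80% power needs (1.960 × 0.6745 + 0.8416 × 0.6564)² / 0.0484 = 72.6, so 73 per arm, and 75 gives 81%. The number fits the immigrant-versus-native gap at beta 0.20. That is neither the stated effect nor the stated beta, and 99% power for that gap would need 168 per arm.

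**The case against.** The best counter-argument is that 47% depends on a two-sided, unadjusted comparison of two proportions, while the Sample size section states neither sidedness nor test. The Analysis section plans longitudinal modelling with determinants included, and Table 1 records drop-out at two follow-ups. Repeated measurements can add information.

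That qualifies the exact figure but does not save the claim. Treating the two follow-ups as fully independent, the most generous case, amounts to 150 observations per arm: (0.15 × √150 − 1.3419) / 0.6764 = 0.732, or 77% power two-sided, and 85% one-sided. Reading 150 as the per-arm number gives the same result. Drop-out as defined largely persists once it has occurred, so the second measurement adds much less than that. A one-sample test of 75 patients against a fixed 45% would give 76% two-sided or 85% one-sided, but this is not a two-arm comparison. No reading reaches 99%.

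Three further objections are fair in part. First, the origin suggested in step 5 is an inference: the document does not say so, 73 is not exactly 75, and the finding does not rest on it. Second, no passage says that a null result will be read as proof of no effect; that is a risk created by the stated beta, not a stated plan. Third, making the risk difference the headline result goes beyond correcting the arithmetic and is a recommendation that can be taken or left.

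**Conclusion.** The concern holds. The sample size, effect, alpha and beta in the Sample size section contradict one another, and no other section amends them. Power at 75 per arm for 45% versus 30% is about 47% two-sided (41% to 49% across methods) or about 60% one-sided, against a stated 99%. The shortfall against the stated beta is roughly fivefold (75 against 378 per arm), and reading beta as 0.10 or 0.20 still leaves the trial far too small.

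The figures assume that the 45% and 30% rates are right, that all 75 patients per arm contribute, and that patients are independent. Loss of patients would lower power, and so would clustering within therapists. The documents give no intraclass correlation. If six therapists per condition in each clinic is read as 24 in all, there are 150/24 = 6.25 patients per therapist. An assumed correlation of 0.01 to 0.05 then gives a design effect of 1 + 5.25 × 0.01 = 1.05 to 1 + 5.25 × 0.05 = 1.26, and two-sided power of about 46% to 39%. This needs correcting because it is the sole stated basis for the size of the primary comparison.

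**What to change.** Replace the power sentence in the Sample size section with figures that agree:

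- 75 per arm gives about 47% power for 45% versus 30% at two-sided alpha 0.05, and 80% power only for 45% versus about 23.5%, in both cases before any allowance for therapist clustering.
- State whether alpha is one-sided or two-sided.
- State that a non-significant result will not be reported as absence of effect. It is advisable to report the risk difference with its 95% confidence interval alongside the planned model, since the expected half-width of about 15 points shows what the trial can and cannot exclude.

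The target in the abstract can stand if 75 per arm is kept. If the sponsor instead wants conventional power for 45% versus 30%, both places must change to at least 163 (80%) or 217 (90%) per arm, again before clustering. That choice is the sponsor's; the abstract says the trial started in January 2010.

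The minimum correction costs only wording and needs no extra patients. The price is that the stated power becomes much less favourable.

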### Analysis

Basic characteristics will be compared between treatment conditions. Dropout will be analysed by (non) parametric longitudinal analysis techniques (eg GLM model) using multivariate statistics. Determinants are modelled along. Analysis will be performed according to the intention-to-treat principle.

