### Recruitment/Setting and locations

Participants are recruited within two outpatient mood disorder clinics in Amsterdam. All new Moroccan and Turkish registries, mostly referred by their general practitioner, are screened on in- and exclusion criteria. If eligible, the new registries are randomized by a research assistant before the intake procedure starts. Then the patients are given an appointment for an intake interview by a therapist from the matching condition. After this intake interview the patients receive study information and the informed consent form from the therapists. Within two weeks after the intake an interviewer contacts a patient by telephone and asks oral consent to participate in the study. If the patient gives permission, an appointment is made for the basic interview in the clinic. If the patient is willing and eligible to participate, a written informed consent is signed.

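### The drop-out model mixes the randomised comparison with determinants measured after intake, so adjusting for them can remove part of the training effect

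*Protocol article*

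**What the plan says.** The Analysis section is short. On the model it says: "Dropout will be analysed by (non) parametric longitudinal analysis techniques (eg GLM model) using multivariate statistics". The next sentence is "Determinants are modelled along", followed by a commitment to intention to treat. No other comparison of the arms on drop-out is described.

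The Background sets out three research questions. Question 1 asks whether training reduces drop-out; question 3 asks what determines drop-out. The Dropout determinants section opens with "Several possible determinants of drop-out will be explored" and lists demographic, clinical and social variables.

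Three places fix the order of events:

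- Recruitment: "the new registries are randomized by a research assistant before the intake procedure starts", and then "Then the patients are given an appointment for an intake interview by a therapist from the matching condition".
- Intervention: among the skills taught is "how to make use of the Cultural Formulation [24] during intake and treatment".
- Assessments: T0 falls in the two weeks following intake; T1 and T2 come 4 and 16 weeks into treatment.

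**The concern.** In a randomised comparison it is safe to adjust for variables fixed before allocation. It is not safe to adjust for variables that allocation can change, because part of the effect may run through them and the model then credits that part to the covariate. The column that Table 1 calls baseline is collected after the patient has met the allocated therapist, and in the intervention arm that therapist has been taught to use the new technique at that very meeting. A better intake could plausibly shift perceived need for care, reported symptoms or reported functioning, and these in turn could affect whether the patient stays.

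The second issue is the length of the list relative to the number of drop-outs. Many covariates on few events make the arm coefficient noisier and, in logistic regression, tend to push it away from the null.

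At stake is the main answer of the trial. With the only stated model serving questions 1 and 3 together, the estimate of the training effect depends on which determinants are included and at which time point, and the article settles neither.

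**Working it through.** **1. Order of events.** Recruitment, Intervention and Assessments together give: randomisation, then intake with a therapist of the allocated arm (trained skill in use), then T0, then T1, then T2. Every determinant collected by interview or questionnaire is therefore recorded after first exposure.

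**2. Which determinants can be affected.** The Dropout determinants section lists 17: age, gender, marital status, education, WHO-DAS II, TIC-P, PNCQ, CIDI diagnosis, IDS, BAI, somatic disease, medication, pain, acculturation, social support, discrimination and mastery.
- Not plausibly changed by one intake: age, gender, marital status, education and lifetime diagnosis, and probably acculturation.
- Measured again later according to Table 1: WHO-DAS II, TIC-P, IDS, BAI and somatic disease at T1 and T2 (5); PNCQ, medication, pain and the Close Person Inventory at T2 (4). That makes 5 + 4 = 9 for which a later value exists. The Analysis section does not say which value enters.

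**3. Events per term.** Inputs from Sample size: 75 per arm, drop-out 45% and 30%. The plan gives no events-per-term figure to reproduce.
- Expected drop-outs: 75 × 0.45 + 75 × 0.30 = 33.75 + 22.5 = 56.25.
- All 17 determinants plus arm, one parameter each: 56.25 / 18 = 3.1.
- If categorical items raise this to 22 parameters (assumed): 56.25 / 22 = 2.6.
- Arm, clinic and four facts fixed before randomisation: 56.25 / 6 = 9.4.

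**4. Precision available.** The pooled normal approximation for 45% against 30% with 75 per arm gives z = (0.15 × √75 − 1.96 × √(2 × 0.375 × 0.625)) / √(0.45 × 0.55 + 0.30 × 0.70) = (1.299 − 1.342) / 0.676 = −0.063, a two-sided power of 47%. The stated 75 per arm does not follow from the stated beta of 0.01, which needs 378 per arm two-sided. That is a separate matter; here it shows only that there is little precision to lose.

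**5. Illustration of the overfitting part (assumed values).** 2,000 simulated trials of 75 per arm, logistic model, 17 pure-noise covariates, true log odds ratio −0.647:

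| | Arm only | Arm + 17 covariates |
|---|---|---|
| Mean log OR | −0.65 | −0.75 |
| SD of log OR | 0.35 | 0.43 |
| Power | 48.2% | 46.9% |
| Type I error | 5.8% | 6.7% |

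The simulation error of a 5% rate is √(0.05 × 0.95 / 2000) = 0.5 percentage points, so the difference in type I error is slight. The loss of precision and the shift away from the null are the visible effects.

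**6. Illustration of the over-adjustment part (assumed values).** One covariate shifted by 0.4 SD by the training, 400,000 simulated patients, drop-out 45% against 30%:

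| Nominal share of the log OR through the covariate | Unadjusted OR | Adjusted OR |
|---|---|---|
| 0% | 0.52 | 0.52 |
| 25% | 0.53 | 0.60 |
| 50% | 0.52 | 0.66 |

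The article contains nothing from which the true share could be estimated.

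**The case against.** The strongest reply is that four words are being read as a full model. The Analysis section does not say which determinants enter, from which time point, whether all enter at once, or whether the adjusted coefficient is the primary result. Since determinants form their own research question and are to be explored, the sentence may describe only that exploratory work. A condensed article also leaves covariate lists to fuller documents.

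Much of this stands, and it rules out several stronger readings:

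- A reader might infer that the training effect will in fact be adjusted for its own consequences. The text permits this but does not say that T1 or T2 values are used, and several listed determinants cannot be altered by an intake. At T0, after a single meeting, any shift is probably small.
- A reader might infer that the model is certainly overfitted. That depends on how many determinants enter together, which is not fixed.
- A reader might infer that drop-outs will be deleted for lack of T1 and T2 interviews. Drop-out itself comes from therapists and medical records, no passage makes later interview answers a required covariate, and such deletion would conflict with the intention-to-treat statement.
- A reader might infer that the T0 alliance and trust scores will be used as covariates. They are secondary outcomes, and nothing says so.

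The two mechanisms also pull in opposite directions: over-adjustment moves the odds ratio towards 1, sparse data move it away. No net bias is shown.

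The reply does not remove the point. The sentence directly follows the description of the drop-out model and most naturally reads as one joint model. It is a stated choice, not merely an omitted detail, and an analysis plan that followed it would carry the problem forward.

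**Conclusion.** The point holds in a conditional form. The only model stated for drop-out combines the randomised comparison with determinants, some of which can change and are first measured after exposure to the allocated therapist. Adjusting for those can remove part of the training effect, and the risk is larger if T1 or T2 values are used. If all 17 determinants enter with arm, there are about 3.1 expected events per term and the estimate loses precision; in the noise-covariate illustration the SD of the log odds ratio rose from 0.35 to 0.43.

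The event count rests on the plan's own rates and sample size and on one parameter per determinant. The simulated figures rest on assumed values and show only what kind of effect is possible. The size and net direction of bias in this trial cannot be derived from the article.

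**What to change.** Separate the two questions in the Analysis section.

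- Question 1, primary: compare drop-out between arms as randomised, adjusted only for clinic and a few prespecified facts fixed before randomisation, for example age, gender, Moroccan or Turkish origin, and generation. State that this arm coefficient is the primary result.
- Question 3, exploratory: a separate model for the determinants, using T0 values, with either a short prespecified list or penalised selection.

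The change is to wording only and needs no new data. Its cost is that the primary model no longer adjusts for severity, so any precision gained from a strongly prognostic symptom score is given up. Randomisation keeps the comparison valid without it.
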